### Intervention

2.6

A single dose of granule therapy is to be administered to both groups within 0.5 h following the onset of an eligible migraine attack. Patients in the treatment group are orally administered SSF granules (2 bags at 7.78 g each, with warm water) within 0.5 h of headache onset. Patients in the control group are orally administered placebo granules (2 bags at 7.78 g each, with warm water) within 0.5 h of headache onset. Both SSF and placebo granules were produced by Sichuan Neo-Green Pharmaceutical Technology Development Company Limited. The placebo was formulated with maltodextrin, coloring agents, bittering agents, and 5% of the SSF herbs to sensorily match the active granules in appearance, taste, and odor, thereby protecting blinding integrity while ensuring negligible pharmacological activity.

Additionally, researchers will provide migraine management counseling to both groups. During the clinical trial period, patients may utilize alternative acute analgesic treatments for headache episodes that do not meet eligibility criteria, provided they contact researchers for treatment registration. In cases where the trial drugs fail to alleviate symptoms during an eligible migraine attack (i.e., no improvement in headache severity, impairments in daily or occupational functioning, or mood alterations), researchers will maintain open communication with patients, permit the use of conventional Western acute analgesics under supervision, and provide guidance on medication administration and post-intervention monitoring. Participants will also be instructed to record the timing and type of rescue medication used.

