#### Primary outcome

2.7.1

The primary endpoint is the proportion of patients achieving headache freedom at 2 h post-dose. Headache freedom is defined as the reduction in headache severity from baseline moderate or severe to no pain, as measured by the VAS.

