### Sample size and recruitment

2.9

The sample size was calculated based on the primary outcome measure (the proportion of patients achieving headache freedom at 2 h post-dose). Sample size determination derived from the treatment effect of 35% versus 11% placebo response (based on unpublished data), calculated through binomial proportion comparison with one-sided *α* = 0.025, *β* = 0.1, and a 24% superiority margin. This calculation yielded a requirement of 60 participants per arm. To accommodate clinical enrollment uncertainties, including anticipated attrition and protocol deviations, the adjusted enrollment target was set at 144 participants, with 72 in each group. Patient recruitment will be conducted through neurology outpatient clinics and poster-based advertising, leveraging the high patient volume across three centers to ensure sufficient enrollment.

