### Statistical analysis

2.11

All statistical analyses will be performed using SPSS 25.0 and R 4.3.1 software. Baseline characteristics will be presented through descriptive statistics [mean ± standard deviation or median (interquartile range) or frequency (percentage)]. For between-group balance testing, independent samples *t*-tests will be employed for normally distributed data with homogeneity of variance, while Mann–Whitney *U* tests are used otherwise. Categorical variables will be analyzed using chi-square tests or Fisher’s exact test based on expected frequencies. All predetermined potential confounders will be included as covariates in subsequent models for adjustment, regardless of their between-group balance status. Additionally, baseline variables showing significant imbalance will undergo sensitivity analyses to assess their confounding effects.

Efficacy analyses will be performed on both intention-to-treat (ITT) and per-protocol (PP) populations, with the ITT set including all randomized participants analyzed according to their allocated groups, regardless of protocol deviations, while the PP set will consist of participants who complied with the trial procedures without major deviations. For efficacy assessment, the use of rescue medication before the 2-h time point will be considered a treatment failure for the primary and key secondary endpoints (e.g., headache freedom, headache relief, absence of most bothersome symptom) (26). Accordingly, participants will be included in the 2-h efficacy analysis only if they have not used rescue medication before that time point, even if medication is taken afterward. Similarly, the assessment of sustained outcomes (e.g., sustained headache freedom at 24/48 h) will require no use of rescue medication within the respective 24/48-h timeframe.

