The primary efficacy endpoint (2-h headache freedom) will be compared between groups using the chi-square test or Fisher’s exact test, with reporting of risk difference (RD) and relative risk (RR) accompanied by 95% confidence intervals (CIs). For secondary endpoints, categorical variables will be analyzed through logistic regression with baseline covariate adjustment, while continuous variables (e.g., VAS scores) will be assessed using a mixed-effects model for repeated measures (MMRM). Time to onset of efficacy will employ Kaplan–Meier curves with the Log-rank test and Cox proportional hazards models to estimate hazard ratios. To address missing data, multiple imputation will be employed under the assumption of missing at random, using fully conditional specification with predictive mean matching for continuous variables and logistic regression for categorical variables, incorporating baseline and post-baseline covariates; 20 imputed datasets will be generated, and results will be pooled using Rubin’s rules. To control for multiplicity, secondary endpoints will be grouped *a priori* into clinically coherent families, each tested using the Holm–Bonferroni method to control the family-wise error rate. The predefined families are: (1) a 2-h symptom response family comprising absence of the most bothersome symptom and headache relief at 2 h; (2) a sustained efficacy family consisting of sustained headache relief and sustained headache freedom from 2 to 24/48 h; and (3) a time-to-event and recurrence family including time to onset of efficacy and headache recurrence rate. Changes in VAS scores and the TCM syndrome score will be analyzed exploratorily and are not included in the adjustment. Safety analyses will be conducted in the safety set (SS), which includes all randomized participants receiving at least one dose of the study medication. This population will be summarized using descriptive statistics for adverse events, vital signs, and laboratory parameters, with between-group comparisons following the methods used for baseline characteristics.

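### Rescue use before 2 h is a treatment failure in one sentence and a ground for exclusion in the next, so the primary and 2-h secondary results depend on which is followed

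*Protocol article*

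**What the plan says.** Three statements in one paragraph of section 2.11 (Statistical analysis) bear on the 2-h denominator:

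- Population: "the ITT set including all randomized participants analyzed according to their allocated groups, regardless of protocol deviations".
- Failure rule: "the use of rescue medication before the 2-h time point will be considered a treatment failure for the primary and key secondary endpoints". The examples given are headache freedom, headache relief and absence of the most bothersome symptom.
- Inclusion rule, in the very next sentence: "participants will be included in the 2-h efficacy analysis only if they have not used rescue medication before that time point". It adds that rescue taken after 2 h does not matter.

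Other sections do not settle which rule governs. Section 2.7.1 defines the primary endpoint without mentioning rescue: "Headache freedom is defined as the reduction in headache severity from baseline moderate or severe to no pain, as measured by the VAS". The 2-h secondary endpoints in section 2.7.2 do not mention it either. The later part of section 2.11 names the test and the effect measures (risk difference and relative risk) but not the denominator.

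Rescue in the treated attack is allowed. If the trial drug does not help, section 2.6 has researchers "permit the use of conventional Western acute analgesics under supervision", with time and type recorded. Table 2 schedules the recording of acute analgesic use at 0.5 h and 1.0 h as well as later.

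**The concern.** The failure rule and the inclusion rule cannot both be applied to the same participant. Under the first, someone who takes rescue at 1 h adds nothing to the numerator and one to the denominator. Under the second, that person appears in neither.

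The inclusion rule selects on an event that follows randomisation and is itself a sign that treatment has not worked. Comparing those who remain is no longer a comparison of the randomised groups. Known failures leave the analysis, response rates rise in any arm where rescue occurred, and the contrast shifts by an amount that depends on how rescue is split between arms. The analysed sample also shrinks. The article does not say whether the planned multiple imputation would apply to the dropped participants, which would be a third possible handling.

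The rule governs the primary endpoint and both members of the first secondary family (relief and absence of the most bothersome symptom at 2 h). If it stays unresolved, the choice could be made after results are known.

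**Working it through.** **Inputs from the article.** Section 2.9: 35% versus 11% headache-free at 2 h, one-sided alpha 0.025, power 90%, 60 per arm required, 72 per arm enrolled.

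**Inputs assumed.** The rate of rescue before 2 h, written r_S (SSF) and r_P (placebo). The article gives none, so a range is shown. The planning rates are taken to hold under the failure rule, so every early rescue user is already counted as a non-responder in them.

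**Step 1: reproduce the stated sample size.** With unpooled variance,

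n = [0.35×0.65 + 0.11×0.89] × (1.960 + 1.282)² / 0.24² = 59.36, so 60 per arm.

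This matches. The planning figures are usable as the baseline.

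**Step 2: rates under each rule.**

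- Failure rule: p_S = 0.35 and p_P = 0.11, with 72 per arm. Risk difference (RD) 24.0 points; relative risk (RR) 0.35/0.11 = 3.18.
- Exclusion rule: numerators are unchanged and denominators shrink, so each rate becomes p/(1 − r) on 72(1 − r) participants.

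For example, with r_S = 10% and r_P = 40%: 0.35/0.90 = 38.9% and 0.11/0.60 = 18.3%, on 64.8 and 43.2 participants.

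Power is the normal approximation Φ[(RD − 1.96·SE₀)/SE₁], with SE₀ the pooled (null) and SE₁ the unpooled standard error.

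| Assumed rescue before 2 h (SSF / placebo) | Rates after exclusion | RD (points) | RR | Analysed | Power |
|---|---|---|---|---|---|
| 0% / 0% (same as failure rule) | 35.0% / 11.0% | 24.0 | 3.18 | 72 / 72 | 93.6% |
| 10% / 10% | 38.9% / 12.2% | 26.7 | 3.18 | 64.8 / 64.8 | 94.5% |
| 20% / 20% | 43.8% / 13.8% | 30.0 | 3.18 | 57.6 / 57.6 | 95.5% |
| 10% / 20% | 38.9% / 13.8% | 25.1 | 2.83 | 64.8 / 57.6 | 89.2% |
| 15% / 30% | 41.2% / 15.7% | 25.5 | 2.62 | 61.2 / 50.4 | 85.1% |
| 10% / 30% | 38.9% / 15.7% | 23.2 | 2.48 | 64.8 / 50.4 | 79.4% |
| 20% / 40% | 43.8% / 18.3% | 25.4 | 2.39 | 57.6 / 43.2 | 78.3% |
| 10% / 40% | 38.9% / 18.3% | 20.6 | 2.12 | 64.8 / 43.2 | 63.0% |

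Under the failure rule, RD, RR and power stay at the first row whatever the rescue rates.

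**Step 3: can the conclusion change?** Suppose 20/72 on SSF and 10/72 on placebo are headache-free. The uncorrected chi-square is 144 × (20×62 − 52×10)² / (72×72×30×114) = 4.21, p = 0.040. Now exclude 7 SSF and 22 placebo rescue users with the same responders, giving 20/65 and 10/50. The chi-square is 115 × (20×40 − 45×10)² / (65×50×30×85) = 1.70, p = 0.19. The counts are illustrative.

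**Step 4: can a difference appear where there is none?** Let true success under the failure rule be 20% in both arms.

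- Rescue 10% SSF, 30% placebo: 0.20/0.90 − 0.20/0.70 = −6.3 points.
- Rescue 30% SSF, 10% placebo: +6.3 points.

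**Step 5: a secondary endpoint.** For relief at an assumed 60% versus 40% with rescue of 10% and 40%, exclusion gives 0.60/0.90 = 66.7% and 0.40/0.60 = 66.7%. A 20-point effect disappears. All four inputs are assumed and happen to cancel exactly, so this shows what is possible, not what is expected.

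**The case against.** The best defence is that the second sentence is loosely worded and not a separate rule. It opens with *Accordingly*, so it is offered as a consequence of the failure rule. Its closing clause serves to say that rescue after 2 h does not void a 2-h result. The next sentence, on sustained outcomes, makes absence of rescue a condition for success. Read together, the passage may mean only that a 2-h responder must not have taken rescue before 2 h. The failure rule also comes first, carries the citation and fits the ITT definition.

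This is plausible as intent, and it supports the fix. It does not rescue the text: inclusion in an analysis is not the same as counting as a responder, and an analyst following the words would drop these participants.

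The objections on size have force. The article gives no frequency of early rescue and no split between arms. More rescue on placebo is a reasonable expectation if SSF works, but it is not a fact in the document. A 10% versus 40% split is an upper-end assumption, and with 10% versus 20% power falls only to 89.2%. The direction is not fixed either: equal rescue raises the RD and leaves the RR alone, an excess on placebo lowers the RR, and an excess on SSF favours SSF. The absence of a stated waiting time before rescue may be condensation in a journal article and is not relied on here; Table 2's recording of analgesic use at 0.5 h and 1.0 h is enough to show that early use is foreseen.

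None of this removes the contradiction. Nor is it a detail left to an unseen analysis plan, since the article states the rule, in two incompatible ways.

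**Conclusion.** The concern holds. As written, section 2.11 gives two incompatible denominators for the primary endpoint and the 2-h secondary endpoints, and the literal exclusion conflicts with the ITT set. The results coincide only if no participant takes rescue before 2 h.

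Across the assumed rescue rates in the table, exclusion moves the planned RD of 24.0 points to between 20.6 and 30.0, the RR from 3.18 to as low as 2.12, and power at 72 enrolled per arm from 93.6% to as low as 63.0%. It can turn a nominally significant result into a non-significant one, or create a difference of 6.3 points in either direction between equally effective arms. These sizes rest on assumed rescue rates and on the planning rates holding under the failure rule. The contradiction rests on neither. Because it affects the primary analysis, it must be resolved before unblinding.

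**What to change.** Delete the sentence in section 2.11 that begins with *Accordingly* and replace it with:

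> Participants who use rescue medication before 2 h remain in the denominator of their allocated arm and are counted as non-responders for all 2-h binary endpoints; rescue after 2 h does not alter the 2-h outcome.

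This keeps the failure rule already stated and agrees with the ITT definition. It also makes clear that early rescue users have a known outcome and are not missing data to be imputed.

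The cost is one sentence. Time and type of rescue are already to be recorded (section 2.6), so no further data are needed. The change concerns the analysis only and leaves the conditions for taking rescue as they are.

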#### Secondary outcomes

2.7.2

The proportion of patients achieving absence of the most bothersome associated symptom (MBAS) at 2 h post-dose. Patients will self-identify their MBAS from the following symptoms at migraine onset: photophobia, phonophobia, nausea, or vomiting.The proportion of patients achieving headache relief at 2 h post-dose. Headache relief is defined as the reduction of initial pain intensity from moderate to severe levels down to mild or no intensity.The proportion of patients sustaining headache relief from 2 to 24/48 h post-dose. Sustained headache relief from 2 to 24/48 h is defined as achieving headache relief without rescue medication use and the absence of moderate-to-severe headache recurrence during 2 to 24/48 h following initial treatment.The proportion of patients sustaining headache freedom from 2 to 24/48 h post-dose. Sustained headache freedom from 2 to 24/48 h is defined as achieving headache freedom without rescue medication use, coupled with the absence of any headache recurrence (mild, moderate, or severe) during 2 to 24/48 h following initial treatment.Change in VAS scores from pre-dose to 0.5, 1, 2, 4, 24, and 48 h post-dose.Time to onset of efficacy, defined as the interval (in minutes) between drug administration and headache relief.Headache recurrence rate between 2 and 48 h post-dose. Headache recurrence is defined as patients who achieved headache relief (freedom) at 2 h post-dose, reexperiencing moderate-to-severe headache (headache of any severity) within the 2 to 48 h post-dose window.Change in TCM “Ying-Wei disharmony syndrome.” The syndrome will be assessed using the Ying-Wei Disharmony Assessment Scale (YWDAS) at baseline, 48 h post-dose, and 7 days post-dose. The scale comprises five core TCM syndromes, and the assessment framework is detailed in Table 3. Its development was grounded in clinical expertise from senior TCM practitioners and integrated classical and contemporary medical literature. Content validity was established through a rigorous review and consensus by a panel of five senior TCM experts. In a pilot study to assess feasibility and inter-rater reliability, all YWDAS assessments were independently performed by two TCM researchers who underwent standardized training using predefined scoring criteria to minimize assessment bias. The inter-rater reliability, assessed by the intraclass correlation coefficient (ICC) for absolute agreement, was 0.76 (95% CI: 0.64–0.84), indicating good agreement.

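### Sustained headache freedom is too sparse on placebo for ordinary adjusted logistic regression: the odds ratio is modestly overstated, and an empty placebo cell would leave the Wald test uninformative.

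*Protocol article*

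**What the plan says.** Section 2.11 (Statistical analysis) fixes one method for all binary secondary endpoints: "For secondary endpoints, categorical variables will be analyzed through logistic regression with baseline covariate adjustment". It also settles how covariates enter: "All predetermined potential confounders will be included as covariates in subsequent models for adjustment, regardless of their between-group balance status". The number of covariates is not given. Missing data are handled with 20 imputed datasets pooled by Rubin's rules. For the primary endpoint the same section allows Fisher's exact test in place of chi-square. It names no sparse-data alternative for the binary secondary endpoints.

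Section 2.7.2 (Secondary outcomes) makes sustained freedom a subset of 2-h freedom: "Sustained headache freedom from 2 to 24/48 h is defined as achieving headache freedom without rescue medication use", and additionally requires that no headache of any severity returns. In Section 2.11 the endpoint belongs to the second of three Holm-controlled families, together with sustained headache relief.

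The planned rates for 2-h freedom are in Section 2.9: "Sample size determination derived from the treatment effect of 35% versus 11% placebo response". The same section states "This calculation yielded a requirement of 60 participants per arm" and then that "the adjusted enrollment target was set at 144 participants, with 72 in each group".

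**The concern.** A subset of an 11% event is rare in an arm of 72. Logistic regression by maximum likelihood has two known weaknesses with few events. The log odds ratio is biased away from zero, more so with each added covariate. And if one arm has no event, the estimate diverges, its standard error becomes enormous and the Wald p-value approaches 1. The second weakness is perverse here, because an empty placebo cell is the result most favourable to SSF.

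The article names neither the estimator nor the test. Rubin's rules, however, combine estimates with their standard errors, which in practice means Wald inference.

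At stake are the effect size, and in unlucky data the test, for an endpoint that carries the durability claim in a multiplicity-controlled family. If an empty cell appeared and the method were changed then, the change would be post hoc.

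**Working it through.** **Inputs from the article.** 2-h freedom 35% on SSF and 11% on placebo; 60 per arm required, 72 enrolled (Section 2.9).

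**Assumed, not in the article.** The share f of 2-h responders who sustain, taken as equal in both arms and varied from 30% to 100%; and 0 to 6 non-prognostic covariates.

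**1. The plan's own figure.** The stated settings are "one-sided *α* = 0.025, *β* = 0.1, and a 24% superiority margin". With unpooled variance, n = (1.96 + 1.2816)² × [0.35 × 0.65 + 0.11 × 0.89] / 0.24² = 10.51 × 0.3254 / 0.0576 = 59.4, so 60 per arm. This reproduces the article (with 24% used as the expected difference) and confirms 11% as the planning rate.

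**2. Expected placebo events.** n × 0.11 × f.
- f = 100%: 72 × 0.11 = 7.9 (60 per arm: 6.6)
- f = 50%: 72 × 0.055 = 4.0 (60 per arm: 3.3)
- f = 30%: 72 × 0.033 = 2.4 (60 per arm: 2.0)

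On SSF at 72 per arm, 25.2, 12.6 and 7.6 events are expected.

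**3. Chance of an empty placebo cell.** (1 − 0.11 f)ⁿ.

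| f | 72 per arm | 60 per arm |
|---|---|---|
| 100% | 0.89⁷² = 0.02% | 0.89⁶⁰ = 0.09% |
| 50% | 0.945⁷² = 1.7% | 0.945⁶⁰ = 3.4% |
| 40% | 0.956⁷² = 3.9% | 0.956⁶⁰ = 6.7% |
| 30% | 0.967⁷² = 8.9% | 0.967⁶⁰ = 13.4% |

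**4. What an empty cell does.** For 10/72 against 0/72, maximum likelihood gives Wald p = 0.999. Fisher's test gives p = 0.0014 and the likelihood-ratio test p = 0.0001. Firth gives a finite odds ratio, (10.5/62.5)/(0.5/72.5) = 24.4.

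**5. Bias of the odds ratio.** Simulation at 72 per arm, 3,000 trials per setting, geometric means, empty-cell trials left out.

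| f | True OR | ML, 0 / 3 / 6 covariates | Excess | Firth |
|---|---|---|---|---|
| 100% | 4.36 | 4.60 / 4.78 / 4.97 | 6 / 10 / 14% | 4.37–4.38 |
| 70% | 3.89 | 4.20 / 4.27 / 4.47 | 8 / 10 / 15% | 3.83–3.89 |
| 50% | 3.64 | 3.95 / 4.08 / 4.32 | 9 / 12 / 19% | 3.53–3.55 |
| 30% | 3.44 | 3.27 / 3.45 / 3.60 | −5 / 0 / +5% | 2.86–2.88 |

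The last row mainly reflects the exclusion of empty-cell trials, which are the ones with the largest effects. It shows no upward bias for maximum likelihood and should not be read as a failing of Firth. A second simulation with 2 or 6 covariates put the excess in the log odds ratio at about 0.07 to 0.16 for f from 50% to 100%.

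**6. Power and type I error at 72 per arm.** Firth's penalised likelihood-ratio test and the Wald test are level at f = 70% to 100%. At f = 50% Firth has 61–65% against 60%, and at f = 30% it has 37–39% against 25%. By exact enumeration without covariates, the two-sided Wald type I error is at most 3.7%, so the test is conservative.

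**The case against.** The strongest reply is that the article says only logistic regression. It names neither maximum likelihood nor the Wald test, and Firth regression is itself a form of logistic regression. The estimator, a sparse-cell rule and the covariate list are details that an article may leave to an SAP that is not shown. This stands in part: nothing in Section 2.11 is contradictory, and a likelihood-ratio test would not break down on an empty cell. But the method is stated, not left open, and Rubin pooling leads to Wald inference by default.

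The second reply concerns size, and much of it stands. With about 4 against 13 events, the standard error of the log odds ratio is √(1/4 + 1/68 + 1/13 + 1/59) = 0.60. The largest bias tabulated at f = 50% is ln(4.32/3.64) = 0.17, less than a third of that. Fisher's test would not rescue power in general: at f = 50% it has 54.3% against 57.4% for Wald, and it gains only in the sparsest setting (26.9% against 23.6% at f = 30%).

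A reader might infer more than the article supports:
- **That an empty cell is likely.** Chances of 11% to 16% arise if 3% against 15% is assumed. That needs 27% of placebo responders to sustain (3/11) but 43% on SSF (15/35), a gap with no basis in the article. Inflation of 26% to 35% needs nine covariates, also unsupported.
- **That all binary secondary endpoints are affected.** Sparsity follows from the planning figures only for sustained freedom. It is not shown for 2-h relief or absence of the most bothersome symptom.
- **That false positive claims become more likely.** They do not; the Wald test is conservative here.
- **That imputation adds a separate failure.** Imputation cannot remove observed events, so an imputed dataset can have an empty placebo cell only if no placebo event was observed. It is the same rare case.
- **That odds ratios beside the primary endpoint's risk difference and relative risk are an error.** This is a reporting preference.

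**Conclusion.** The point holds for sustained headache freedom at 24 h and 48 h, and the harm is modest. The ceiling of about 8 expected placebo events rests only on the article's own figures. Everything beyond it depends on the assumed sustaining share and number of covariates. Within those assumptions, ordinary maximum likelihood with 2 to 6 covariates overstates the odds ratio by roughly 7% to 19% when half or more of the responders sustain. The empty-cell breakdown is negligible if nearly all sustain and becomes material only at about 40% or below. Its effect on the p-value presumes Wald inference, which is inferred from Rubin's rules and not stated. Meaningful loss of power is likewise confined to low sustaining shares. The primary endpoint is not touched. The change is worth making because it is cheap before unblinding and awkward afterwards.

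**What to change.** In Section 2.11, state that sustained headache freedom from 2 to 24 h and from 2 to 48 h will be analysed by Firth penalised logistic regression, with penalised likelihood-ratio p-values and profile penalised-likelihood intervals. Add a pooling rule for the 20 imputed datasets that suits likelihood-based inference, since pooling estimates and standard errors would bring Wald inference back. Ordinary logistic regression may stay for the commoner binary secondary endpoints. A standardised risk difference and relative risk could be added so that sustained freedom reads on the same scale as the primary endpoint, but this is optional.

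The cost is a few lines of text. R 4.3.1 is already named, and no extra patients or data are needed. The downside is slightly shrunken estimates and a method less familiar to some readers.

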**Conclusion:**

The findings are anticipated to deliver high-quality evidence validating SSF’s efficacy and safety, offering a promising therapeutic alternative for acute migraine attacks.

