#### Exclusion criteria

2.3.4

Participants meeting any of the following criteria will be excluded:

Patients with ≥15 migraine days within the past 4 weeks.Patients who have used analgesics for ≥10 days within the past 4 weeks.Patients with secondary headaches attributed to organic pathologies, including but not limited to subarachnoid hemorrhage, cerebral hemorrhage, cerebral infarction, vascular malformations, arteritis, hypertension, or atherosclerosis.Patients with severe circulatory, digestive, respiratory, or hematopoietic system diseases or cancer.Patients with a history of epilepsy, stroke, other neurological disorders, or psychiatric conditions.Patients with severe liver diseases, or those presenting with abnormal liver function, defined as aspartate aminotransferase (AST) or alanine aminotransferase (ALT) levels greater than 1.5 times the upper limit of the normal range (ULN).Patients with severe kidney diseases, or those presenting with abnormal kidney function, defined as creatinine (Cr) levels exceeding the ULN.Patients exhibiting significant anxiety or depression symptoms [Hamilton Anxiety Rating Scale (HAMA) ≥15 scores or Hamilton Depression Rating Scale (HAMD) ≥18 scores].Patients with cognitive impairment, manifested as an inability to read or comprehend assessment scales, non-compliance with medical treatment, or inability to complete efficacy evaluations.Patients using migraine prophylaxis at stable doses for <3 months.Patients who are pregnant, lactating, or planning pregnancy.Patients currently participating in other clinical trials.

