
## Conclusion

4

In conclusion, this trial will provide robust evidence on the efficacy and safety of SSF for the treatment of acute migraine attacks. The findings, whether demonstrating positive, neutral, or negative outcomes, will hold substantial clinical relevance for migraine management.

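### The between-group safety tests have little power to detect harm at 72 or fewer dosed per arm, so a non-significant result cannot support the article's wording on safety

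*Protocol article*

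**What the plan says.** Protocol article, section 2.11 (Statistical analysis), defines the safety set as randomised participants who took study medication. Adverse events, vital signs and laboratory values in that set are summarised descriptively, "with between-group comparisons following the methods used for baseline characteristics". Earlier in 2.11 those methods are given as tests of baseline balance: t-test or Mann-Whitney U for continuous variables, and chi-square or Fisher's exact test for categorical ones, chosen by expected frequencies. For the primary endpoint the same section specifies a risk difference and relative risk with 95% confidence intervals. It names no interval for any safety comparison.

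Section 2.8 provides for AE and SAE monitoring, with laboratory tests, vital signs and ECG at baseline and 48 h. Table 2 extends AE and SAE collection to 7 days. Section 2.6 sets a single dose. Section 2.9 sizes the trial on 2-h headache freedom alone: "This calculation yielded a requirement of 60 participants per arm", and "the adjusted enrollment target was set at 144 participants, with 72 in each group".

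The abstract states: "The findings are anticipated to deliver high-quality evidence validating SSF’s efficacy and safety". Section 4 states that "this trial will provide robust evidence on the efficacy and safety of SSF for the treatment of acute migraine attacks". The limitations in section 3 mention the single-dose design only for long-term prophylactic potential and cumulative effects. They do not mention limited safety information.

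**The concern.** A test of baseline balance asks whether two groups differ by more than chance. For safety, the useful question is how large an excess risk the data leave open, and a p-value does not answer it. In a trial sized for a 24-point efficacy difference, a non-significant safety test is the likely result even when a real excess exists.

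For laboratory values, the named tests compare group location. A rank test gives the largest value the same weight whether it lies just above the next one or several times higher, so a few marked rises in one arm barely move it.

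At stake is the published safety statement. A set of safety tables without significant differences, next to wording about validated safety, invites a conclusion that one dose in at most 72 people cannot support.

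**Working it through.** **Inputs.** From section 2.9: 35% against 11%, one-sided α = 0.025, β = 0.1, 60 per arm required, 72 per arm enrolled. From section 2.6: one dose. From section 2.3.5: participants without an eligible attack in 45 days are withdrawn, at a rate not given, so 72 is the ceiling of the safety set. I also show 60; the dosed number could be lower still. The event rates in step 3 and the 1% rate in step 4 are assumptions.

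**1. The plan's own figure.** The unpooled normal approximation gives (1.960 + 1.282)² × (0.35 × 0.65 + 0.11 × 0.89) / 0.24² = 59.4, so 60 per arm. The stated figure reproduces as an ordinary superiority test against zero difference. It concerns efficacy only; no safety figure is stated.

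**2. Events needed for significance.** With k events on SSF and none on placebo, and n per arm, two-sided Fisher p = 2 × C(n,k) / C(2n,k). With fewer than 10 events in total, the expected count per arm is below 5, so Fisher applies under the usual rule (the article states no cut-off).

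| Events | p, n = 72 | p, n = 60 |
|---|---|---|
| 1 vs 0 | 1.0 | 1.0 |
| 3 vs 0 | 0.245 | 0.244 |
| 5 vs 0 | 0.058 | 0.057 |
| 6 vs 0 | 0.028 | 0.027 |

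Six against none is the smallest such split with p < 0.05.

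**3. Power for a true rate of 10% against 2%.** Sum the product of the two binomial probabilities over all pairs of counts with Fisher p ≤ 0.05. Result: 0.379 at 72 per arm and 0.277 at 60. If the analysis switches to an uncorrected chi-square once there are 10 or more events in total, the same sum gives 0.45 and 0.32. Either way, a fivefold excess is missed more often than found.

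**4. What zero events allow.** The two-sided 95% upper limit is 1 − 0.025^(1/n).
- n = 72: 1 − 0.025^(1/72) = 0.0499, or 5.0%.
- n = 60: 1 − 0.025^(1/60) = 0.0596, or 6.0%.

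A reaction with a true rate of 1% has a 0.99^72 = 0.485 chance of not appearing in 72 people, and 0.99^60 = 0.547 in 60.

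**5. Against the wording.** Steps 2 to 4 show that a table with no significant difference, or with no events at all, is compatible with harm rates of several percent after one dose.

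**The case against.** The strongest reply is that the tests are only one part of the safety assessment. The sentence in 2.11 puts descriptive summaries first, 2.8 and Table 2 provide AE and SAE monitoring to 7 days, and 2.10 requires final review of anomalous data before database lock. A marked enzyme rise can be recorded and reported as an adverse event whatever a group test shows. This stands. A reader might infer that safety is judged by the tests alone, or that isolated serious changes cannot surface in this trial; the article supports neither. The weakness is in the between-group tests.

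Second, nothing in the article says that p > 0.05 will be read as safety. The abstract speaks of an expectation, and section 4 goes on to allow for positive, neutral or negative findings. This also stands: the risk lies in pairing weak tests with strong wording and is not a stated decision rule.

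Third, a reader might infer that raw 48-h values are compared without regard to each participant's baseline. The article does not say so; the named tests could be applied to changes. It leaves the matter open.

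Fourth, the limits in steps 2 to 4 apply to any trial of this size, and shift tables and listings usually belong in an SAP. Their absence is no finding here. But the article itself chose the comparison method and the wording of the claim, and both can be judged as written.

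**Conclusion.** The point holds in a limited form and is minor. Section 2.11 fixes between-group safety tests that, at 72 or fewer dosed per arm, have little ability to detect harm: 6 against 0 events are needed for p < 0.05, power for 10% against 2% is about 38% with Fisher's test, and zero events leave rates up to about 5% open. A non-significant result cannot support validated safety (abstract) or robust safety evidence (section 4), and section 3 does not list this as a limitation.

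The 10% and 2% rates are illustrative. The figures at 72 assume that everyone randomised is dosed, so they are the favourable case. The primary analysis is untouched.

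**What to change.** In 2.11, keep the descriptive summaries and replace the baseline-type tests for safety by:

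- AE and SAE incidence per arm, with the risk difference and exact 95% confidence intervals;
- comparison of change from baseline, or of baseline-adjusted 48-h values, for laboratory values and vital signs;
- the number of participants per arm with marked laboratory abnormalities at 48 h. The entry limits in 2.3.4 (AST or ALT above 1.5 times ULN, creatinine above ULN) can serve as descriptive cut-offs. They are exclusion limits, not defined safety thresholds. Baseline may precede dosing by 45 days or more and rescue analgesics are allowed, so a crossing is not automatically due to the dose.

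State that p > 0.05 is not evidence of safety. Reword the abstract's conclusion and section 4 to short-term tolerability of a single dose, and add the limited safety sample to the limitations in section 3.

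The cost is a few more tables from data already collected and a less favourable safety statement.
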